#### 2.8.1. Chemical Taste Perception

Chemical taste perception is evaluated by the taste strips test. Taste sensitivity evaluation is necessary for a proper diagnosis and subsequent treatment of taste disorders [30]. Through the taste strips test, it is possible to obtain a total score and identify those patients with taste alterations such as parageusia (incorrect taste identification) and hypogeusia or ageusia (decreased taste sensitivity or lack of taste, respectively) from those with normogeusia (normal perception of taste). Once patients have been diagnosed, the changes that have arisen from the beginning to the end of the intervention and the differences observed with the different treatment groups are to be evaluated.

The taste disturbance prevalence ranges from approximately 20 to 86% [31], which occurs approximately 2–3 weeks after the start of cancer therapy and persists throughout the treatment [32]. These distortions often contribute to difficulties maintaining food intake during treatment [33], thus increasing the risk of malnutrition [28]. As chemical test perception is complementary to electrical taste perception, the consumption of the miraculin-based food supplement might enhance food intake and improve nutrition status due to better food taste perception.

#### 2.8.2. Smell Perception

Taste and smell disorders (TSD) can occur during the course of cancer, and they are associated with anorexia, early satiety, weight loss, malnutrition, and reduced quality of life [34]. Odor food perception is possible through two pathways: the orthonasal pathway, which occurs when odors are perceived directly through the nose, and the retronasal pathway, which occurs when odors are released from food during mastication and reach the olfactory receptor cells in the nose [35]. It has been estimated that 80% of the smell information of a meal is transmitted through retronasal olfaction [36], and it is commonly associated with the sense of taste due to its contribution to the flavor of foods or drinks. However, the orthonasal odor perception pathway is usually more affected than the retronasal pathway in different clinical conditions, with intact retronasal perception in the absence of orthonasal olfactory function [37]. This could be due to the difference in vulnerability between the anterior and posterior olfactory epithelium.

Approximately 60% of patients with disorders in smelling also complain about disorders of taste [38]. These two processes are tightly related; however, they are often described as separate entities due to patients having difficulty identifying them [39]. Since the prevalence of dysosmia is approximately 5–60% in cancer patients undergoing chemotherapy [4], its assessment is essential to complete the taste and smell perception evaluation. In this sense, an improvement in TSD may ameliorate the general food intake and, therefore, the quality of life and nutritional status of patients undergoing active cancer treatment. Orthonasal olfactory function is measured by the Sniffin’ Sticks test, identifying patients with normosmia and hyposmia depending on their age, and is measured in the same visits as the taste tests (v1, v3, v4, v5).

#### 2.8.3. Nutritional Status

Malnutrition is the state resulting from a lack of intake or uptake of nutrition that leads to changes in body composition, reduced fat-free mass and body cell mass, decreased functional capacity, and impaired clinical outcome from disease [40]. This can result from starvation, disease, or aging combined or as separate entities [41]. However, when malnutrition is caused by a concomitant disease, it is referred to as disease-related malnutrition (DRM), where inflammation is usually present [42].

Malnutrition is a condition that is highly prevalent in cancer patients. It is estimated that up to 10–20% of cancer patients die due to malnutrition rather than the tumor [43]. This appears as a consequence of both the tumor and the antineoplastic treatments and negatively affects the quality of life and the effectiveness of treatments. Thus, the assessment of nutritional status in cancer patients is crucial to improve disease prognosis.

Nutritional status is evaluated by the GLIM criteria at the beginning and the end of the intervention (3 months), a period where it is possible to assess the nutritional intervention effect. From the assessment of the nutritional status, a diagnosis of the type of malnutrition presented (moderate or severe) is obtained. Additionally, the nutritional status of the patients will be evaluated at visits 3 and 4 to evaluate the evolution of the patient throughout the clinical trial. For the rest of the variables, the average change occurring from the beginning to the end of the intervention between the different treatments is evaluated.

According to the practical guidelines for clinical nutrition in cancer, nutritional intervention has to lead to increasing oral intake in cancer patients who are malnourished or at risk of malnutrition [43]. In addition to dietary advice, the nutritional intervention is intended to treat symptoms and derangements impairing food intake (e.g., dysgeusia) and offering oral nutritional supplements (ONS) when necessary. In this regard, it is possible that improvement in taste distortions has a positive effect on food intake and, therefore, on the nutritional status of cancer patients.

#### 2.8.4. Morphofunctional Assessment

Morphofunctional assessment consists of a series of evaluations that determine body composition and functionality. These evaluations include classic parameters (anthropometric parameters, biochemical parameters, food intake) and emerging parameters (bioelectrical impedance, nutritional ultrasound, dynamometry, functional tests and biochemical parameters) [44]. The realization of these measurement techniques certainly allows phenotypic categorization and etiologic criteria for malnutrition diagnosis via the GLIM criteria.

Assessment for DRM diagnosis and severity is based on five criteria: three phenotypic criteria (unintentional weight loss, low body mass index, and reduced muscle mass) and two etiologic criteria (reduced food intake or assimilation and inflammation or disease burden) [23]. In addition, each of its evaluations provides information that allows a predictive analysis of nutritional status evolution and prognosis. Therefore, morphofunctional evaluation provides vital information to assess the evolution of nutritional status based on the assigned treatment. Morphofunctional assessment will be measured in the main visits to support monitoring of nutritional status. However, each of these tests individually also provides information on the adequacy of nutritional treatment.

##### Anthropometric Parameters

Even though body weight is not sensitive enough for the early detection of DRM, unintentional weight loss is basic to estimate nutritional requirements, and it is an important screening tool for DRM risk as well as the simplest phenotypic criteria for the diagnosis of malnutrition [45].

Weight losses of 5–10% in the last 6 months or 10–12% in more than 6 months point to moderate malnutrition, while losses >10% in the last 6 months or >20% in more than 6 months point to severe malnutrition [23]. Thus, body weight (kg) and percentage weight loss (%) were measured at the main visits (v1, v3, v4, and v5). Changes that occurred each month are to be evaluated using the mean of the change and compared between treatments to evaluate its evolution throughout the clinical trial.

Because weight loss can be modified by alterations in hydration status (edemas) [46], body mass index (BMI) was calculated. BMI is an anthropometric measure widely accepted for body composition measurement that, even with its limitations (does not measure fat, muscle, or skeletal compartments), is used as a phenotypic criterion for malnutrition diagnoses. BMI values < 20 kg/m^2^ for patients under 70 years and <22 kg/m^2^ for patients over 70 years old point to moderate malnutrition, while severe malnutrition corresponds to BMI values < 18.5 kg/m^2^ in patients under 70 and <20 kg/m^2^ in patients over 70 years old [23]. In cancer patients, weight change and BMI, as well as nutritional intake, are recommended to detect nutritional disturbances at an early stage [43]; therefore, they were evaluated throughout the entire study. BMI was measured at the main visits as well (v1, v3, v4 & v5).

Waist circumference (WC), another anthropometric parameter, together with waist-to-height ratio has been suggested as a stronger predictor for several cancers [47]; they are central adiposity, visceral fat, and chronic disease risk factor indicators and are used as cardiometabolic morbidity and mortality predictors [48]. Recommended waist circumference cutoffs are used to monitor the health risk (>102 cm for men and >88 cm for women) [49] in cancer patients. WC and waist-to-height ratio were measured at the main visits (v1, v3, v4, and v5). Changes occurring in anthropometric parameters are to be evaluated using the mean of the change and compared between treatments to evaluate its evolution throughout the clinical trial.

##### Electrical Bioimpedance

The presence of diseases can produce an increase in body water and/or fat mass without weight loss. Indeed, patients can lose >10% of their body weight over three to six months and have a BMI above or in a normal range [50]. Therefore, body composition measurements are essential for adequate nutritional status assessment. Body composition is to be evaluated via electrical bioimpedance (BIA). This technique estimates the indirect body composition by running a small electrical current through the body and measuring the resistance to body tissues [51]. BIA provides objective information about body compartments (fat-free mass and fat mass) and hydration status (total body water (TBW), extracellular (ECW), and intracellular water (ICW)). Indirect muscle data such as the Appendicular Skeletal Muscle Index (ASMI), Fat-Free Mass Index (FFMI), and Appendicular Lean Mass (ALM) were also measured. From these parameters, it is possible to obtain the body composition of the cancer patient and complete their nutritional assessment. In this sense, low ASMI (<6 in females, <7 kg/m^2^ in males) is used as an indicator of muscle mass loss, one of the phenotypic criteria for malnutrition diagnosis [23].

On the other hand, the raw bioelectric parameters from BIA are to be obtained via direct measurement, without interference of anthropometric factors (weight or age). Through resistance (R) and reactance (Xc), it is possible to obtain the phase angle (PhA). This BIA parameter is an important indicator of cell membrane health and integrity and has been considered a marker of clinical conditions such as cancer [52,53]. A low PhA indicates a poorer nutritional status, as well as impaired cell membranes and muscle function, and may be an important prognostic factor of survival in cancer patients [54]. Indeed, high PhA was significantly associated with lower mortality in cancer patients. A cutoff point was identified using the ROC curves for PhA in cancer patients (≤5.6°) [55]. After adjusting for sex and age, it is possible to obtain the standardized PhA, which is an independent prognostic indicator in cancer patients receiving chemotherapy [56]. Even though the standard cutoff value for standardized PhA has not yet been established [57], changes in the patient over time can be considered changes in nutritional status.

BIA performance is to be carried out at scheduled visits v1, v3, v4, and v5. Changes that occurred in BIA parameters month by month were evaluated using the mean of the change and compared between treatments to evaluate the evolution.

##### Dynamometry

Dynamometry is a functional method to assess muscle strength through handgrip strength [44]. Hand dynamometry is a general marker for nutritional status and is considered a support measure for the assessment of muscle mass, a phenotypic criterion for the diagnosis of malnutrition [23]. Malnutrition implies a reduction in muscle mass, which is reflected in lower performance on functional tests and alterations in body composition [58]. Dynamometry assessment is of special interest because the decrease in muscle strength appears before changes in anthropometric measurements and laboratory parameters are observed. Muscle strength measurement is a useful tool in screening and assessing malnutrition [59] and sarcopenia [60]. Low grip strength is a predictor of longer hospital stays, poor health-related quality of life, and increased functional limitations [61].

Reference values for dominant hand muscle strength to assess DRM have been obtained for the Jamar^®^ dynamometer in a Spanish population [62], and they are to be used in the clinical trial to identify those patients with low grip strength as a support measure in the malnutrition diagnosis and sarcopenia risk. Based on age and sex, patients are to be classified as normal or with low grip strength (<27 kg in males, <16 kg in women) [63]. Hand dynamometry is to be carried out at scheduled visits v1, v3, v4, and v5. Changes occurring in grip strength are to be evaluated using the mean of the change and compared between treatments to evaluate its evolution.

##### Nutritional Ultrasound

Nutritional ultrasound is an emerging technique that uses ultrasound to assess body composition. It is composed of two techniques, i.e., muscle ultrasound (FFM assessment) and adipose ultrasound (FM evaluation). The muscle ultrasound method quantifies muscle modifications in malnutrition and provides information on functional changes [64]. In this sense, the anterior rectum area of the quadriceps can be used as a criterion for malnutrition, and it has been observed that a high rectus femoris cross-sectional area is associated with a decrease in mortality risk in cancer patients. A cutoff rectus femoris cross-sectional area (≤4.47 cm^2^/m^2^) and rectus femoris-*Y*-axis (≤1.3 cm) are identified in cancer patients [55] and used to evaluate changes in muscle composition. The measurement of the rectus femoris muscle of the quadriceps also correlates with force and functional execution or performance tests [65].

Malnourished cancer patients with taste distortion and consuming the miraculin-based food supplement are expected to improve their body composition from baseline (v0) to the end of the intervention (v5). The mean of the difference between the scores found between these visits is to be statistically compared with those found in the rest of the treatments.

##### Functionality Test

Timed-up-and-go (TUG) is a functional test that evaluates physical function through the time a patient takes to rise from a chair, walk three meters away, turn, walk back, and sit down again [66]. This functional test can predict fall risks and mortality [67]. A functional assessment of patients is important for nutritional status evaluation and sarcopenia diagnosis. The final purpose is the functional recovery of the patient, with positive changes in weight, FM, FFM, and functionality [44]. To evaluate the activity and monitor any clinical changes over time, the TUG test is to be assessed at v1, v3, v4 and v5. It used sarcopenia cutoff points for low performance (≥20 s) [60,68]. Malnourished cancer patients with taste distortion and consuming the miraculin-based food supplement are expected to improve functionality from baseline (v0) to the end of the intervention (v5). The mean of the difference between the scores found between these visits will be statistically compared with those found in the rest of the treatments.

#### 2.8.5. Diet

Inadequate dietary intake is an important factor involved in the weight loss and progressive functional decline associated with advanced cancer [69]. Reduced food intake is a well-established indicator of malnutrition that has strong validity. In this sense, less than or equal to 50% of energy requirements for more than one week, any reduction for more than 2 weeks, or any chronic gastrointestinal condition that adversely impacts food assimilation or absorption is considered reduced food intake or reduced assimilation, an etiologic criterion for malnutrition diagnosis [23].

Diet is collected in the 72 h food daily record at v1, v3, v4 and v5, allowing the transformation of food consumption into energy intake, water, macronutrient intake (proteins, fats (total fat, saturated (SFAs), monounsaturated (MUFAs) and polyunsaturated fatty acids (PUFAs), carbohydrates, fiber, and micronutrient intake (vitamins and minerals)). From this information, it is possible to calculate the caloric and lipid profile as well as the coverage of the recommended intakes of the population. Obtained data are to be evaluated using the European Food Safety Authority dietary reference values [70] and the Nutritional Objectives of the Consensus Document of the Spanish Community Nutrition Society [71]. If food intake does not meet energy requirements, a high-calorie, high-protein oral nutrition supplement with fiber, EPA, DHA, beta-glucans, and enriched in L-leucine (no added sugars) will be prescribed.

Dietary habits, diversity and variety will be measured using a quantitative FFQ. To evaluate the overall dietary habits, the consumption frequency of all food items will be categorized as meeting or not meeting the criteria of the dietary guidelines for the Spanish population [72], the food pyramid for the Spanish population [73], and the nutrition goals for the Spanish population [71].

Malnourished cancer patients with taste distortion and consuming the miraculin-based food supplement are expected to improve their dietary intake from baseline (v0) to the end of the intervention (v5). The mean of the difference between intake and food frequency found between these visits will be statistically compared with those found in the rest of the treatments. The evolution of diet will also be evaluated through the different intervention visits where it will be measured (v1, v3, v4, and v5).

#### 2.8.6. Physical Activity

Resting energy expenditure is increased in many cancer patients; however, total energy expenditure appears to be lower because of a reduction in daily physical activity [74]. In cancer patients, total energy expenditure may be estimated from standard formulas for resting energy expenditure and standard values for physical activity level [75]. To calculate the total energy expenditure and energy requirements, physical activity is evaluated. Maintenance or an increase in the physical activity level to maintain physical function, muscle mass, and metabolic pattern is a clinical practical recommendation in cancer patients [43]. Increased physical activity reduces the risk and improves survival of patients in several cancers [76].

To calculate the energy balance, the energy intake obtained in the 72 h daily food record is to be compared with the total energy expenditure calculated from the Institute of Medicine, Food and Nutrition Board [77], plus the energy derived from physical activity obtained through the International Physical Activity Questionnaire [78]. Physical activity will be evaluated at the beginning (v0) and at the end of the intervention (v5). The mean of the difference between intake and food frequency found between these visits will be statistically compared with those found in the rest of the treatments. The evolution of diet will also be evaluated through the different intervention visits where it will be measured (v1, v3, v4, and v5).

#### 2.8.7. Quality of Life

Malnutrition negatively impacts quality of life and oncologic treatment. Thus, nutrition plays a crucial role in heterogeneous cancer care. In patients undergoing (adjuvant) radiotherapy, nutritional support improves nutritional status but also some aspects of quality of life [79]. In patients with advanced cancer, where life expectancy is several months or years, deficits in nutritional status may impair performance status, tolerance treatments, quality of life, and survival [43]. The European Organization for Research and Treatment of Cancer Quality of Life Questionnaire-Core30 (EORTC QLQ-C30) used in the present clinical trial has a strong prognostic value for the overall survival of cancer patients [80]. In cancer patients, taste alterations are present for a long time [81], suggesting that the risk of malnutrition and low quality of life could continue once the treatment is finished.

Quality of life is to be evaluated at the beginning (v1) and at the end of the intervention (v5). The mean difference between these visits will be compared with the rest of the treatments. The evolution of quality of life will also be measured on v1, v3, v4, and v5.

#### 2.8.8. Tolerance and Adverse Events

Nausea, diarrhea, dysphagia, vomiting, constipation, and abdominal pain are gastrointestinal symptoms that are used to measure product consumption tolerance. However, they are also considered supportive indicators that can impair food intake or absorption, an etiological criterion used for malnutrition diagnosis [23]. Symptoms of intensity, frequency, and duration will be collected in a diary sheet throughout the study and evaluated at every visit, and the percentage change between visits will be compared between treatments. Gastrointestinal disorders will be judged using Common Terminology Criteria for Adverse Events (CTCAE) from the National Cancer Institute [82]. These adverse events will be used to discern the severity of food intake or absorption impairment and evaluate tolerance to the nutritional intervention. CTCAE will be evaluated at the beginning (v1) and end of the intervention (v5), and the percentage change between these two visits will be compared between treatments. Evolution will also be measured on v1, v3, v4, and v5.

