##### Oral and Intestinal Microbiota and Metagenomics

The microbiota or microbiome refers to all microbial organisms that naturally exist within an ecosystem, i.e., part of an organism such as the oral cavity, the intestine, or the vagina. The concept of the microbiome refers not only to the members of the microbial ecosystem but also encompasses their collective functional capacity (metagenome) and activity (metabolome), including interactions within the community and with the host. Indeed, the metagenome is a term used to design the collective genome representative of the many microorganisms existing in a particular ecosystem, and metagenomics is the systematic study of the assemblages of genomes for those microorganisms.

Currently, much attention has been given to the oral microbiome and oral and systemic health [120]. The mouth has a variety of microbes second only to the gut in the complexity of human sites. Differences in the oral microbiome occur with old age, which may be due to oral conditions and diseases, e.g., cancer and other chronic diseases [121]. Many factors contribute to the salivary microbiome profile. In particular, radiotherapy for the treatment of head and neck cancer can cause tissue damage and specifically the salivary glands, causing an alteration in the composition of saliva accompanied by dermatitis, oral mucositis, xerostomia, dysgeusia, dysphagia, and dysbiosis [122]. The latter is related to changes in the quantitative and qualitative composition of the microbiota, mainly increased cariogenic cocci and yeast populations [123]. These changes may lead to altered host–microbe interactions or homeostatic imbalance that can contribute to a disease state, often with inflammation [124]. Recently, the oral microbiome has been suggested to be an explanatory factor for nasopharyngeal carcinoma prognosis. Lower within-community diversity is associated with higher mortality, and certain measures of between-community diversity are related to mortality [125]. Additionally, recent data suggest a potential association of the oral microbiome with mutational changes in oral squamous cell carcinoma [126]. Therefore, modifications in oral biofilms of irradiated patients improving dysgeusia, such as treatment with miraculin, could contribute to better oral health.

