#### 3.4.7. Tolerance and Adverse Events

A diary sheet is given where the patient writes down the possible adverse events, symptoms presented, symptoms date (beginning and end), intensity (mild, moderate, intense), a possible relationship with the product (yes, no, it is possible) and behavior adopted. On every visit, the patient is also asked about any other discomforts not written down because they are considered light and related to product consumption. Gastrointestinal disorders such as abdominal distension, abdominal pain, nausea, regurgitation or gastroesophageal reflux, vomiting, constipation, diarrhea, and flatulence are defined and recorded based on Common Terminology Criteria for Adverse Events (CTCAE) from the National Cancer Institute [82]. These adverse events are classified as Grade 0 (not described), Grade 1 (mild), Grade 2 (moderate), Grade 3 (severe), Grade 4 (mortality risk), and Grade 5 (death associated with an event).

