## 5. General Characteristics of the Population

This section presents very preliminary results of the clinical trial. For the present study a total of 62 patients were evaluated for eligibility. Of them, 31 met the selection criteria and were randomized into three intervention groups (Figure 5). During follow-up, there were 10 dropouts, mainly due to the consumption of the supplement distorted the taste of some non-sweet acidic foods (n = 6) and because of the prescription added difficulty to their, already complex, antineoplastic treatment (n = 2). A final sample of 21 patients completed the clinical trial.

The sample was made up of 61.9% women and 38.1% men with a mean age of 59.8 ± 11.65 years old, all of them undergoing active treatment with chemotherapy and taste alteration measured by electrogustometry (Table 3). The average body mass index was 22.37 ± 3.67 kg/m^2^, classifying the patients as normal weight. However, the weight lost in the last 3 months was −7.60 ± 5.76%, with no significant differences between treatment groups. 

The most prevalent type of cancer was colorectal cancer (28.6%) followed by breast, lung, pancreas and liver cancers, each with 9.5%. Fasting glycemic control (105 ± 19 mg/dL) was within the normal reference parameters (74–106 mg/dL). The insulin concentration (12 ± 10 µU/mL) was normal in the entire population (3–25 µU/mL) as well as the lipid profile. All patients had systemic inflammation (CRP > 5 mg/dL). Both vitamins and minerals were found within the reference values except for vitamin D, which means blood concentration (21.25 ± 13.86 ng/mL) was insufficient (range 15–30 ng/mL).

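### The stated between-arm tolerance comparison covers gastrointestinal symptoms and does not count product-related taste distortion or stopping for intolerance, although taste distortion is the main recorded reason for dropout

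*Protocol article*

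**What the plan says.** Section 2.8.8 of the protocol article names the tolerance measure: "Nausea, diarrhea, dysphagia, vomiting, constipation, and abdominal pain are gastrointestinal symptoms that are used to measure product consumption tolerance". It then sets out two comparisons.

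- **Diary symptoms.** Their intensity, frequency and duration are "collected in a diary sheet throughout the study and evaluated at every visit, and the percentage change between visits will be compared between treatments".
- **CTCAE.** The scope is given as "Gastrointestinal disorders will be judged using Common Terminology Criteria for Adverse Events (CTCAE"), and the comparison across arms as "CTCAE will be evaluated at the beginning (v1) and end of the intervention (v5), and the percentage change between these two visits will be compared". The course over v1, v3, v4 and v5 is also to be described.

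Section 3.4.7 describes the instrument. CTCAE recording is illustrated with this list: "Gastrointestinal disorders such as abdominal distension, abdominal pain, nausea, regurgitation or gastroesophageal reflux, vomiting, constipation, diarrhea, and flatulence are defined and recorded". The same section provides an open diary for any adverse event, with dates, intensity and possible relation to the product, and an open question at every visit. Section 3.2 (malnutrition criteria) repeats the six symptoms of section 2.8.8.

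Section 2.2 says that patients who leave will be asked whether an adverse event of the tablets was the reason. Section 5 reports 31 randomised, 10 dropouts and 21 completers, and explains the dropouts as "mainly due to the consumption of the supplement distorted the taste of some non-sweet acidic foods (n = 6").

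**The concern.** A tolerance outcome should register the reasons for which patients cannot stay on the product. Here the compared outcome is built from gastrointestinal symptoms, while the document's own account of dropout points mainly to a taste effect of the tablet. Two features act together.

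1. The event is not a component of what is compared between arms.
2. The main CTCAE contrast needs a v5 value, so patients who stopped because of the event are not in it.

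Followed as written, the tolerance result would describe gastrointestinal symptoms, largely in those who stayed. Section 6 also intends the trial to identify the dose with the greatest benefit. The product works by altering the taste of sour food, so an unwanted version of that effect could plausibly differ between the two strengths. A dose conclusion presented beside a tolerance comparison that omits it would be incomplete.

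A smaller matter is that the symptom lists do not agree, so a reader cannot tell which set defines the outcome.

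**Working it through.** **Inputs (section 5):** 31 randomised, 10 dropouts, 21 completers, 6 dropouts for taste distortion, 2 because the prescription added to an already complex treatment.

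**Step 1, reproduce the stated figure.** 31 − 10 = 21 completers, as the article says. The text gives reasons for 6 + 2 = 8 of the 10 dropouts.

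**Step 2, size of the uncounted event.** Exact (Clopper-Pearson) limits for x of n are the 2.5% quantile of Beta(x, n − x + 1) and the 97.5% quantile of Beta(x + 1, n − x).

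| Quantity | x/n | Estimate | Exact 95% CI |
|---|---|---|---|
| Taste distortion among dropouts | 6/10 | 60% | 26% to 88% |
| Taste-distortion dropout among randomised | 6/31 | 19.4% | 7.5% to 37.5% |
| Any dropout among randomised | 10/31 | 32.3% | 16.7% to 51.4% |

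**Step 3, who can enter the v1-to-v5 contrast.** At most the completers can: 21/31 = 67.7% of those randomised. Section 2.12 handles a missing value by reducing the sample size for that variable, so a patient who left is simply absent. All six taste-distortion dropouts are therefore outside this contrast, whatever symptoms it lists. They may contribute to diary and intermediate-visit summaries up to the time they left, but under section 2.8.8 those summaries concern gastrointestinal symptoms.

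**Step 4, do other stated measures fill the gap?** The Taste and Smell Survey (section 3.4.1) concerns changes since the onset of illness. The visual-analogue questionnaire (section 3.4.6) asks whether a taste change is noticed after the product. Its scale runs from not at all or very bad to very good or very effective, so a strong unwelcome change could receive a high score on that item. Neither is described as a tolerance outcome.

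**Step 5, compare the symptom lists.**

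| Item | 2.8.8 and 3.2 | 3.4.7 (CTCAE) |
|---|---|---|
| Nausea, vomiting, diarrhea, constipation, abdominal pain | yes | yes |
| Dysphagia | yes | not named |
| Abdominal distension | no | yes |
| Regurgitation or reflux | no | yes |
| Flatulence | no | yes |

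Five items are shared, one is named only in sections 2.8.8 and 3.2, and three only in section 3.4.7.

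**The case against.** The strongest reply is that safety capture is wider than the gastrointestinal list. The diary in section 3.4.7 is open and records relation to the product. Every visit includes an open question, and section 4.2.1 hands out a record sheet for adverse effects separate from the tolerance sheet. Section 2.2 asks leavers about adverse events, and section 2.14 makes the medical team responsible for evaluating unintended effects. Section 5 itself shows that taste-distortion dropouts were noticed, counted and published. A reader might infer that the trial has no means of recording taste distortion, and the documents do not support that. What stands is narrower: none of this information enters a stated between-arm tolerance comparison.

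Second, the list in section 3.4.7 is introduced as examples. A reader might infer that dysphagia is never graded. That is not established, because section 2.8.8 calls dysphagia a gastrointestinal symptom and says gastrointestinal disorders are judged by CTCAE. The mismatch is a matter for reconciliation.

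Third, by-arm adverse-event and withdrawal tables are often left to an analysis plan, which is not shown. That is fair for the tables as such. The point here rests on what section 2.8.8 does state: which symptoms measure tolerance and which changes are compared.

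Fourth, the dropouts are a result and are known only in hindsight. That limits the remedy for data collection in this trial. It does not prevent analysing and reporting what was recorded.

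**Conclusion.** The point holds in this limited form. The tolerance comparison stated in section 2.8.8 does not count product-related taste distortion or withdrawal for intolerance. Its v1-to-v5 part also excludes everyone who dropped out. The event concerned accounts for 6 of 10 dropouts and 6 of 31 randomised patients (19.4%, exact 95% CI 7.5% to 37.5%). These figures rest on section 5 as printed and on each patient having one main reason for leaving.

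Two further inferences should be resisted. The text does not say which arms the six patients were in, and the flow diagram is not shown. No rate for the active arms, and no difference between doses, can therefore be derived. Nor do the documents show that oral mucositis or dry mouth belong in the product's tolerance list. The article describes radiotherapy damage to the salivary glands as "accompanied by dermatitis, oral mucositis, xerostomia, dysgeusia, dysphagia, and dysbiosis", and attributes none of this to the tablets.

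The list disagreement is real but minor. This is a change that should be made, mainly to analysis and reporting; it does not invalidate the trial.

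**What to change.** In section 2.8.8, add two components to the tolerance outcome: product-related taste distortion, taken from the diary and the recorded reasons for stopping, and withdrawal for intolerance. Report by arm, with all randomised patients as the denominator, the number with each event at any time and the number who stopped because of it. Keep the v1-to-v5 change alongside, with the number of patients contributing to it, and place these counts next to any statement about dose.

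Reconcile the symptom lists in sections 2.8.8, 3.2 and 3.4.7 so that one list defines both the outcome and the CTCAE recording. State whether dysphagia, abdominal distension, reflux and flatulence belong to it.

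The cost is a few rows in a table, since reasons for stopping and product relationship are already collected. The downside is a less favourable tolerance profile. Because section 5 suggests that follow-up is complete, any new diary items would serve only the later efficacy studies. In this trial, unprompted diary entries may understate distortion among patients who stayed.
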